**Primary objective**

The aim of the study is to evaluate whether tonsillectomy performed with an IDTS is non-inferior compared to tonsillectomy performed with cold steel instruments in terms of PTH and postoperative pain.

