**Method**

*Design*

The project is designed as a Danish randomized controlled multi-center trial of tonsillectomy by conventional cold steel surgical technique versus IDTS. The study is blinded for patients until six months after surgery and the study is assessor blinded.

Randomization is computerized via the tonsil database and utilizes block randomization for each department in a random table of 2000 with equal numbers of group assignments. The randomization is only apparent to the surgeon on the day of the surgery and the day before.

*Course*

All elective and acute patients referred to tonsillectomy, with or without adenoidectomy, on benign indications will be assessed for eligibility at the participating ENT departments. Given a signed declaration of consent patients will be enrolled and randomized in the study to either the standard cold steel tonsillectomy or to IDTS tonsillectomy.

After surgery all patients will be brought to the recovery room for 1-4 hours or hospitalized for a day. Before hospital discharge a surgeon will check for postoperative hemorrhaging and the patient and caregivers will receive oral and written recommendations for the postoperative period. Patients or caregivers are requested to follow the recommendations, and they are instructed to contact the ENT department or to call an ambulance, if postoperative hemorrhage occurs.

There will be no planned postoperative visits at the hospital. During the first six postoperative months included patients/caregivers are asked to complete electronic questionnaires online on their mobile device: daily, for the first two postoperative weeks, and again one month and six months postoperatively.

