**Power Considerations:** The sample size calculation is based on data from the Danish Tonsil Database. In a twelve months period, the frequency of PTH causing reoperation with hemostasis was 7.9%. With an expected non-inferiority treatment difference between the IDTS and the cold steel instrument, a significance level of 0.05, a power of 80%, and a non-inferiority limit of 4%, the required sample is 1126 patients. Assuming a drop out frequency of 10% into account, a total of 1250 patients are required. With a non-inferiority limit set to 4%, the present study will be able to detect a clinically relevant change in the frequency of PTH causing reoperation with hemostasis.

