**Statistical analysis**

Endpoints will be evaluated as differences between treatment groups. Categorical data are analyzed by chi2 or Fisher’s exact test. Depending on normal distribution, continuous data is analyzed by either un-paired Student’s *t-test* or Mann-Whitney rank sum test. An Intention-to-treat principle will be used including all randomized participants in the analysis. Stratification will be performed, and confounding factors (sex, age, surgical indication, BMI, smoking, comorbidity) analyzed in a multiple logistic regression model. Repeated measurement data will be analyzed in a mixed effect model for repeated measurements (ANOVA) with group and time as systematic factors and patients as random effect. The model takes random variations over time into account. Post-hoc tests will be based on the Kenward-Roger approximation to test all included patients despite missing data. The significance level is set at 0.05.

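### Intention-to-treat of all randomised patients is the only analysis set named for a non-inferiority claim on PTH; a per-protocol analysis should stand beside it

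*Protocol*

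**What the plan says.** The Primary objective section asks whether IDTS tonsillectomy is "non-inferior compared to tonsillectomy performed with cold steel instruments in terms of PTH and postoperative pain". Power Considerations sets the PTH margin and the size: "a significance level of 0.05, a power of 80%, and a non-inferiority limit of 4%, the required sample is 1126 patients". It then allows for loss: "Assuming a drop out frequency of 10% into account, a total of 1250 patients are required".

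The Statistical analysis section names a single analysis population: "An Intention-to-treat principle will be used including all randomized participants in the analysis". No per-protocol or as-treated set appears anywhere in the protocol. There is also no rule for a patient operated on with the other technique, a patient never operated on, or a patient whose PTH status is unknown. The one statement on missing data, about the Kenward-Roger approximation, belongs to the repeated-measures model and does not reach the binary PTH endpoint.

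Randomisation comes before the operation. Under Course in the Method section: "Given a signed declaration of consent patients will be enrolled and randomized in the study". Under Design: "The randomization is only apparent to the surgeon on the day of the surgery and the day before".

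**The concern.** In a superiority trial, analysing everyone as randomised tends to work against the claim, because any mixing of the treatments pulls the difference toward zero. In a non-inferiority trial the same pull works for the claim. If IDTS truly causes more bleeding, an IDTS patient who is converted to cold steel carries a lower risk into the IDTS arm. Patients who are never operated on cannot bleed after surgery, so keeping them in both denominators lowers both rates and with them the gap.

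The design leaves room for both. Allocation is made after consent and is visible to the surgeon by the day before surgery, so a patient can be randomised and then cancelled or converted. At stake is the chance of declaring IDTS non-inferior when it is worse by the full margin. With one analysis set, nothing written in the protocol would show that such a result came from dilution.

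**Working it through.** **Inputs from the protocol.** Control PTH rate: "the frequency of PTH causing reoperation with hemostasis was 7.9"% (Power Considerations). Margin 4 points, significance level 0.05, power 80%, 1126 patients before and 1250 after dropout (same section). Equal allocation: "in a random table of 2000 with equal numbers of group assignments" (Design). Hence 625 per arm.

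**Inputs assumed.** The protocol gives no rate of conversion or of randomised patients not operated on, so 2%, 5% and 10% are shown. Converted patients are given the full cold-steel risk.

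**Step 1: reproduce the sample size.** With 7.9% in both arms and a one-sided 0.05 test,

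n per arm = (1.645 + 0.842)² × 2 × 0.079 × 0.921 / 0.04² ≈ 562.3, rounded up to 563, so 1126 in total.

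This matches exactly. One-sided 0.025 would need 714 per arm (1428 in total) and does not match, so one-sided 0.05 is the test to assess. For dropout, 1126 / 0.9 = 1251.1, or 1252 when rounded up to equal arms, against the stated 1250. In reverse, 1250 × 0.9 = 1125.

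**Step 2: false non-inferiority rate.** Let the true rates be c = 0.079 (cold steel) and e = 0.119 (IDTS), a difference exactly at the margin. For an unpooled Wald test,

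P(declare non-inferiority) = Φ[(0.04 − (e* − c*)) / SE − 1.645], with SE = √[(c*(1 − c*) + e*(1 − e*)) / 625],

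where c* and e* are the expected rates in the intention-to-treat analysis.

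- No dilution: e* − c* = 0.04, so the result is Φ(−1.645) = 5.0%.
- A share k of IDTS patients converted to cold steel: c* = 0.079, e* = (1 − k)(0.119) + k(0.079).
- A share k of each arm counted as event-free: c* = (1 − k)(0.079), e* = (1 − k)(0.119).

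Worked for k = 10%:

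- Conversion: e* = 0.115, difference 0.036, SE = 0.0167, Φ(0.239 − 1.645) = 8.0%.
- Event-free: c* = 0.0711, e* = 0.1071, difference 0.036, SE = 0.0161, Φ(0.249 − 1.645) = 8.1%.

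| Share k | Expected difference | Converted, IDTS to cold steel only | Counted event-free, both arms |
|---|---|---|---|
| 0% | 4.00 points | 5.0% | 5.0% |
| 2% | 3.92 points | 5.5% | 5.5% |
| 5% | 3.80 points | 6.4% | 6.4% |
| 10% | 3.60 points | 8.0% | 8.1% |

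A binomial simulation gave similar values: 5.2% with no dilution, 6.6% and 8.3% at 5% and 10% conversion, and 8.5% at 10% event-free.

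**Step 3: dropouts excluded.** If patients with unknown PTH status are left out and are missing at random, c* and e* are unchanged, the difference stays at 4.0 points and the rate stays at 5.0%. Only the precision falls.

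**The case against.** The strongest reply is that the protocol does nothing wrong by choosing intention-to-treat, and that a statistical analysis plan, which is not at hand, may define a per-protocol set. Both are fair. Intention-to-treat belongs in the decision, and a full definition of further sets is ordinary analysis-plan content. What remains is that the protocol itself fixes the population for its non-inferiority question, and that population alone is weak protection for that question.

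A reader might go further and infer that the 10% dropout allowance contradicts the intention-to-treat statement. It does not. Enlarging a trial for expected missing outcomes while analysing patients as randomised is routine, and imputation or likelihood methods can reconcile the two.

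A reader might also take the 10% as the share that will be scored as free of PTH, add 10% conversion from IDTS, and arrive at a false non-inferiority rate of about 12%. The protocol states no such scoring rule and no conversion rate. The caption of Figure 2 says that a physician enters PTH in the database, so a patient who stops answering questionnaires need not lose PTH status.

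Three further points stand:

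- The calculations place the true difference exactly at the margin, which is the case the test must guard against. At a true difference of zero, conversion does not bias the estimate.
- Patients converted because of difficult bleeding may keep a high risk, and the dilution would then be smaller than shown.
- A per-protocol set can itself favour IDTS. Suppose the 10% of IDTS patients who are converted have 20% PTH within an arm rate of 11.9%. The rest then have (11.9 − 0.1 × 20) / 0.9 = 11.0%, the per-protocol difference is 3.1 points, and that analysis alone would pass falsely about 13% of the time. This argues against replacing intention-to-treat, not against adding a second analysis.

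**Conclusion.** The point holds as a cheap improvement. The protocol tests non-inferiority on PTH with a single as-randomised analysis set, and both conversions and never-operated patients would move a truly inferior IDTS result toward the claim.

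The direction is clear when IDTS is truly worse; the size is not known. With 2% to 10% of patients affected by one of the two mechanisms, the false non-inferiority rate rises from 5% to between about 5.5% and 8%. That rests on assumed shares, true rates of 7.9% and 11.9%, 625 per arm and a one-sided 0.05 test. If the only loss is dropout that is excluded and random, there is no inflation. The documents do not support calling intention-to-treat an error, or the dropout allowance a contradiction.

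**What to change.** In the Statistical analysis section:

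1. Keep the as-randomised intention-to-treat analysis of PTH.
2. Add a per-protocol analysis of PTH, restricted to patients operated on with the assigned technique only and with known PTH status at 30 days.
3. Claim non-inferiority on PTH only if the upper confidence limit of the difference is below 4 points in both analyses.
4. State that a missing PTH status is not counted as no PTH by default, and is taken from the physician-entered database where possible.

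The Introduction says the database already holds surgical method and instruments, so the cost is one extra analysis on data being collected. There are two downsides. Power is slightly lower because both analyses must pass: with no true difference, 625 per arm gives about 84% and 563 per arm gives the planned 80%, so the joint requirement cannot exceed the lower of the two. The per-protocol set also has its own selection bias, which is why it supplements intention-to-treat and does not replace it.

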**Table 1:** Overview of measurements, timing, and definitions.

**Table 2:** Overview of data entered in the online register by both physician and patients.

**Figure 1:** Participating ear, nose and throat departments in Jutland are: Aalborg University Hospital and Thisted Hospital. Gødstrup Hospital. Esbjerg Hospital. Lillebælt Hospital, Vejle. Sønderjyllands Hospital, Sønderborg.

**Figure 2:** Eligible patients who have signed a written consent are included in the study. Patient information is entered into the tonsil database by the surgeon. The computer randomly assigns patients to two study arms via block randomization. The control group undergoes standard cold steel tonsillectomy. The investigational group receives tonsillectomy with impedance dependent tissue sealer device. The per-operative procedure is equal for both groups as well as postoperative recommendations. The patients or their caregivers answer daily questionnaires on their mobile device regarding adherence to postoperative recommendations; pain scores on a Likert scale for adults/Wong-Baker scale for children; activity level; food consumption; unscheduled contacts to the health care system; return to school, work or childcare; satisfaction with the procedure; health related quality of life on the EQ5D-SL questionnaire; and quality of taste and smell. If post-tonsillectomy hemorrhage, infection, rehospitalization for rehydration occurs the doctor will input a detailed account in the database.

**Randomized controlled trial on Cold Steel versus Impedance Dependent Tissue Sealer tonsillectomy comparing postoperative morbidity**

Authors: [name]^1^; [name]^1^; [name]^3^; [name]^4^; [name]^5^; [name]^6^; [name]^1,2^.

Affiliations: 1 University Clinic for Balance, Flavour and Sleep, ENT department Gødstrup, [name], 2 Department of Clinical Medicine, Aarhus University, [name], 3 Ear, nose and throat department, Aalborg University Hospital, [name]; 4 Ear, nose and throat department, Sygehus Sønderjylland, [name], 5 Ear, nose and throat department, Sygehus Lillebælt, [name], 6 Ear, nose and throat department, Sydvestjysk Sygehus, [name].

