**Introduction**

Tonsil surgery, with or without adenoidectomy, performed on both children and adults is one of the most frequent surgical procedures in the ear, nose and throat (ENT) specialty worldwide, and the number of tonsil operations has increased over recent decades^1–5^. In Denmark, approximately 7.000 tonsil operations are performed annually^6^ based on benign indications such as recurrent episodes of acute tonsillitis and upper airway obstruction due to adeno-tonsillar hypertrophy^7^.

Although, commonly performed, tonsil surgery is associated with significant morbidity^3^, such as postoperative pain and more severely post tonsillectomy hemorrhage (PTH)^7–12^. Postoperative pain lasts for approximately two weeks, and may in severe cases result in delayed discharge, a visit at the emergency department or readmission for pain control, hydration, and treatment of possible underlying infection^3^. The incidences of PTH vary between 0.3 and more than 10%^1,11,13,14^ and is a major and potential life-threatening complication of tonsil surgery^3,8^.

Because the evidence base of tonsil surgeries in Denmark is low, it is recommended in the Danish National Clinical Guideline from 2019^15^ , to secure the monitoring of tonsil surgeries via a uniform registration of procedures and diagnoses in Denmark. Further recommendations^15^ are that tonsil surgeries are monitored via a database, that can register the surgical method, the extent of the surgery (tonsillectomy vs. tonsillotomy), and length of postoperative hospital stay which is not properly described in Danish patients^15^. The criteria for offering patients tonsil surgery vary in Denmark, and the diagnostic criteria are not well-defined for especially recurrent acute tonsillitis and chronic tonsillitis^15^. There is also believed to be a variation in the applied surgical techniques especially on which instruments are used for the removal. Such data can be obtained from properly designed clinical databases^16^.

The Danish Tonsil database is a population based clinical database established in 2017 in the Central Denmark Region. It is a copy of the concept underlying The National Tonsil Surgery Register in Sweden (NTSRS), which was founded in 1997 covering more than 80% of all tonsil surgeries in Sweden. Several retrospective studies based on data from the register have been published^8,17^.

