**Outcome Assessment**

Primary endpoints:

- Incidence of PTH defined as hemorrhage requiring hemostasis with bipolar electric coagulation, ligature, compression and/or medical treatment with anti-fibrinolytic within the first 24 hours after surgery (early PTH) until 30 days after surgery (late PTH).
- Intraoperative blood loss assessed by a standardized protocol utilizing the gravimetric method. The nurse suctions up 100 ml of NaCl weighed on the scale for precision (Kern & Sohn, PCB 6000-1). The suction canister is also weighed on the scale, as well as the dry gauze. After the surgery the canister of blood including the NaCl is weighed and the dry weights of the canister and gauze including the NaCl are subtracted, this leaves the total blood loss of the operation. It is assumed that 1 gram blood = 1 ml blood.
- Operative time in minutes from the Boyle-Davis gag is placed until it is removed. The operating nurse is responsible for measurements of time.
- Postoperative pain is assessed on an 11-point numeric rating scale ranging from 0 “no pain” to 10 “worst possible pain”. For children, the Wong-Baker Faces rating scale will be used.

Secondary endpoints:

- Patient reported: Unscheduled contacts to the health care system, patient satisfaction, health related quality of life, and patient reported quality of smell and taste via a validated TASTE questionnaire, followed by further investigation should the patient report altered taste at six months.

Variables:

- Patient reported outcome measures (PROMs) of postoperative recovery (return to normal diet, physical activity, and return to work, school, or childcare), compliance to postoperative recommendations.

**Inclusion criteria:** First time tonsillectomy due to; Tonsillar hypertrophy, recurrent tonsillitis (including previous peritonsillar abscess), chronic tonsillitis, systemic complications to tonsillitis, other (mononucleosis), PFAPA (periodic fever, aphthous stomatitis, pharyngitis, cervical adenitis), tonsillar plugs, peritonsillar abscess and signed written consent.

**Exclusion criteria:** Diseases in the hematopoietic system, antithrombotic or anticoagulant drugs in the recovery period, suspicion of or known malignancy, patients, or parents unable to read or speak Danish, patients, or parents unable to use online application for self-evaluation, patients or parents unable to give informed consent, body weight under 16 kilograms.

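### The repeated-measures model, as worded, reduces pain to one constant group difference, with no group-by-time term and no defined time window

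*Protocol*

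**What the plan says.** The protocol's Statistical analysis section describes one model for all repeated measurement data, a mixed model "with group and time as systematic factors and patients as random effect". Two further statements follow: "The model takes random variations over time into account", and "Post-hoc tests will be based on the Kenward-Roger approximation to test all included patients despite missing data". The section names no group-by-time term, no residual covariance structure and no contrast for the post-hoc tests.

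The Primary objective section asks for non-inferiority in PTH and pain. Outcome Assessment lists pain as a primary endpoint, "Postoperative pain is assessed on an 11-point numeric rating scale ranging from 0" to 10 for adults; "For children, the Wong-Baker Faces rating scale will be used". It states no day, window or summary measure.

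On timing, the Method section schedules questionnaires "daily, for the first two postoperative weeks, and again one month and six months postoperatively". The legend to Figure 2 ties pain to the daily ones: "The patients or their caregivers answer daily questionnaires on their mobile device regarding adherence to postoperative recommendations; pain scores on a Likert scale". The Method section also says that randomisation is blocked within each department.

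**The concern.** The protocol itself expects pain to run a course: "Postoperative pain lasts for approximately two weeks". A difference between two surgical techniques therefore need not be constant over the diary period. A model with group and time as separate factors assumes that it is constant and returns one number.

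Three things are at stake.

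- **Dilution.** A difference limited to part of recovery is pulled towards zero. Where the aim is non-inferiority, that is the direction of the favourable conclusion.
- **Unstable weights.** Diaries will not all be complete. The additive model then sets the weight of each day by the pattern of missing entries, so the quantity estimated is not fixed in advance.
- **Missing terms.** Adults and children use different scales and randomisation is blocked by department, but neither enters the model. Randomisation protects the group comparison from bias, so the cost is precision.

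The Kenward-Roger sentence is a separate misattribution. Kenward-Roger adjusts standard errors and degrees of freedom. Patients with incomplete diaries stay in the analysis because the likelihood uses all available data, under missing at random.

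**Working it through.** The protocol gives no figure for the pain model, so there is none to reproduce. Its sample size of 1126 is for PTH; half of it, 563 per arm, is used where a sample size is needed. All SDs, correlations and dropout rates below are assumptions, because the protocol gives none for pain.

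**1. What the additive model estimates, complete data.** The group effect is the plain mean of the occasion-specific differences.

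| True difference | 14 occasions | 16 occasions |
|---|---|---|
| 1 point, days 1-14 | 14/14 = 1.00 | 14/16 = 0.875 |
| 1 point, days 1-7 only | 7/14 = 0.50 | 7/16 = 0.44 |
| 1 point, days 1-3 only | 3/14 = 0.21 | 3/16 = 0.19 |
| +1 on days 1-5, -1 on days 8-12 | (5 - 5)/14 = 0 | (5 - 5)/16 = 0 |

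Even with 16 occasions, days 1-14 hold 14/16 = 87.5% of the weight.

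**2. What it estimates with incomplete diaries.** Take the same missing pattern in both arms and within-patient correlation r. Each score from a patient with m entries then has weight 1/(1 + (m - 1)r). Let 40% stop after day 7 of 14, with r = 0.4.

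- Completers: 1/(1 + 13 × 0.4) = 1/6.2 = 0.161 per score.
- Early stoppers: 1/(1 + 6 × 0.4) = 1/3.4 = 0.294 per score.
- Days 1-7: 7 × (0.6 × 0.161 + 0.4 × 0.294) = 1.50.
- Days 8-14: 7 × 0.6 × 0.161 = 0.68.
- Share of days 1-7: 1.50/(1.50 + 0.68) = 69%, against 50% with complete data.

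The same formula gives 62.5% at r = 0 and 70% at r = 0.8. With 20% stopping it gives 56% to 60% over that range of r.

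**3. Standard error of the averaged difference, complete data.** Let S be the true covariance matrix over T occasions, v its mean variance and c its mean covariance. The random-intercept model gives variance (2/n)(v + (T - 1)c)/T. Since v + (T - 1)c equals the sum of all elements of S divided by T, this is (2/n) × sum(S)/T², the true variance. With a falling SD and serial correlation (profile A below, 563 per arm) both standard errors are 0.0915. The simulated type I error over 2000 null trials is 0.0495.

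**4. Standard errors at single days.** The additive model has no separate single-day group difference. Suppose group-by-time is added and the random intercept kept. The model then uses one pooled SD, the root mean square of the daily SDs, for every day. On the early days the type I error is 2(1 - Φ(1.96 × pooled SD/early SD)).

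- Profile A: SD 2.3 on days 1-9, then 2.2, 2.1, 2.0, 1.8 and 1.6 to day 14, 0.8 at one month, 0.4 at six months.
- Profile B: SD 2.4 on days 1-7, falling by 0.2 a day to 1.0 on day 14, then 0.7 and 0.5.

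| SD profile | Occasions | Pooled SD | Pooled/early SD | Early-day type I error |
|---|---|---|---|---|
| Constant | 14 or 16 | same | 1.00 | 5% |
| A | 16 | √(67.46/16) = 2.05 | 0.89 | 8% |
| A | 14 | √(66.66/14) = 2.18 | 0.95 | 6% |
| B | 16 | √(60.10/16) = 1.94 | 0.81 | 11% |
| B | 14 | √(59.36/14) = 2.06 | 0.86 | 9% |

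Under profile A with 16 occasions the model gives 0.122 on every day. The true values are 0.137 on day 5, 0.095 on day 14, 0.048 at one month and 0.024 at six months.

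**The case against.** Interactions, covariance structures and contrasts are often left to the SAP, which is not at hand. The protocol does not exclude an interaction, and the sentence "The model takes random variations over time into account" may refer to a further variance term. An average over recovery is also a legitimate quantity to estimate, and the days 1-14 mean proposed here dilutes too: 1 point on days 1-7 becomes 0.50, and equal and opposite early and late effects still cancel.

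Part of this stands. The proposed mean does not cure dilution, so the daily differences must be shown with it. What it adds is a defined window and fixed weights. The SAP argument is weaker. The protocol states a model, and an added variance term would not supply a group-by-time effect, so an SAP would have to change the specification and not only complete it.

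A reader might infer more than the text supports:

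- **That pain is averaged over days 1 to 180.** Pain is tied explicitly only to the 14 daily questionnaires, Table 1 is not shown, and the average is by occasion, not by calendar time.
- **That the planned model gives wrong single-day standard errors.** It gives no single-day differences. The error needs an added interaction, a retained random intercept and a variance that changes by day.
- **That a run of unadjusted daily tests is planned.** The post-hoc contrasts are not named.
- **That the Kenward-Roger sentence invalidates the handling of missing data.** A mixed model does use incomplete diaries; only the reason given is wrong.

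**Conclusion.** The point holds in a limited form. As worded, the model yields one constant group difference for a primary endpoint with no stated window. The size follows from counting occasions: a 1-point difference in the first week is reported as 0.50 over 14 complete occasions or 0.44 over 16. With incomplete diaries the day weights move, to 69% on days 1-7 in the example with 40% stopping and a correlation of 0.4, both assumed.

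The averaged standard error is valid with complete data. An early-day type I error of about 8% to 11% (16 occasions) or 6% to 9% (14 occasions) would arise only under the conditions in step 4 and the two assumed SD profiles; with constant SD it is 5%. Leaving out department and scale costs precision. The Kenward-Roger sentence should be corrected but changes no result. The protocol states a non-inferiority limit only for PTH, so these shifts cannot be translated into a changed conclusion on pain. The wording should be amended before analysis; the trial's data are not compromised.

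**What to change.** For pain, specify a repeated-measures model over days 1-14:

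- Fixed effects: group, categorical time, group-by-time, department, scale/age group and scale-by-time.
- Covariance: unstructured, with heterogeneous Toeplitz or AR(1) as the stated fallback if it does not converge.
- Pain contrast: the equally weighted mean difference over days 1-14, with its confidence interval.
- Beside it, the day-by-day differences, labelled descriptive or Holm-adjusted, because the mean alone can hide opposite early and late effects.
- Any one- and six-month pain scores: reported separately.

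Reword the missing-data sentence to say that the likelihood model uses all available diary data under missing at random, and that Kenward-Roger only adjusts standard errors and degrees of freedom.

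The cost is analysis wording and slightly more model fitting. No new data or patients are needed.
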